##### Sleep quality

FBSS-associated sleep quality disturbance was assessed by the Pittsburgh Sleep Quality Index (PSQI). The PSQI questionnaire is composed of 19 items that yield 7 component scores, each component yields a score ranging from 0 to 3, with 3 indicating the greatest dysfunction. A total score of >5 is identified as disordered sleep [27].

##### Analgesic consumption

Celecoxib will be the only available analgesic, and the total amount was divided by the follow-up period to detect the daily requirement at each follow-up interval. The investigators will also offer free consultation during the trial and use tablets returned every follow-up interval to increase the participants’ compliance.

### Adverse events

Common adverse events (AEs) in acupuncture clinical trials include subcutaneous hematoma, fainting, continuous post-needling pain, and allergies at the sites of needle insertion [28]. Patients with any undesirable effect during the trial will be advised to contact their acupuncturists. The acupuncturists will treat the adverse reactions immediately and contact relevant researchers. All the details (include the time of occurrence, symptoms, duration of symptoms) of AEs will be reported by researchers in the case report forms (CRFs) and the ethics committee immediately. Participants have the rights to take any medical treatment to alleviate uncomfortable symptoms whether it is or not caused by the intervention. The ethics committee of Shanghai Municipal Hospital of Traditional Chinese Medicine takes responsibility for deciding whether to suspend the trial once any AE occurs. After accessing and investigating the cause of adverse events, relevant free medical treatment and appropriate financial compensation will be made to participants.

### Withdrawal

Investigators will evaluate the participants who find their low back pain cannot be alleviated by acupuncture (base on a NRS score ≥6) or have serious AEs (severe infection, coma, shock) to discontinue the study. Furthermore, participants can discontinue the treatment at any time for any reason. All discontinued participants’ data will be treated as missing data.

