### Inclusion criteria

Individuals will be recruited for the study if they satisfy the following criteria:

1. Aged 18–80 years

2. Primary diagnosis of FBSS [19] (in this study, FBSS is defined as low back and leg pain persist or recur for at least 6 months following at least one decompression and/or fusion procedure) and not requiring further surgery

3. Average low back pain score ≥6 on a 0–10 numerical rating scale (NRS)

4. On a stable dose of pain medications for at least 2 weeks prior to screening and willing to decrease the pain medication dose during the study

5. No evidence of failure to improve substantially with conservative management including but not limited to physical therapy, acupuncture, exercises, drug therapy, and bedrest

6. Willing to prohibit any treatment that may affect trial results other than acupuncture treatment

7. Competent to understand the study protocol and volunteer to write informed consent to participate

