#### Primary outcome measurement

The primary outcome measure is the pain intensity of the low back assessed using an 11-point numerical rating scale (NRS) [9]. Patients will record their low back pain two times per day on a diary for 3 days prior to assessment. The pain intensity for each assessment was calculated as the average NRS available during that period.

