### Data collection and management

Clinical data will be collected using the printed CRFs, which will be stored securely in a locked cabinet in the office at the hospital. Two independent investigators will enter the data into the clinical trial management platform ResMan and check for double entry to ensure the accuracy of data [29]. All electronic datasets will be de-identified and password protected. Both paper files and electronic documents are accessed to only authorized researchers. After verification, the database will be locked and delivered for statistical analysis. All original CRFs and consent forms will be kept strictly confidential and preserved for 10 years after publication. Only if there exists a life-threatening emergency event when it is a must to know the allocated intervention which participant has received, unblinding is permissible and the researcher can reveal the allocated details in the sealed envelope. Once unblinding occurred, the participant should be discontinued in the trial and the investigator should record the reason for the discontinuation in CRF.

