### Statistical analysis

Statistical analyses will be performed using SAS (version 9.4) by an independent statistician totally blinded to the group allocation. All data will be analyzed based on the intention-to-treat principle, including the missing data from dropouts which will be substituted into the collected data in the last assessment. For measurement data, if the data is in conformity to normal distribution and homogeneity of variance, data values will be presented as mean ± standard deviation (*MD*±*SD*) and covariance analysis will be applied to compare data between groups. If the data does not comply with the normal distribution, median (P25, P75) will be adopted to describe it and the Mann-Whitney *U* nonparametric test will be applied for the comparison between groups. For categorical data, data can be presented as frequency, composition ratio, or rate on the basis of data results. When it comes to dichotomous or unordered multinomial data, the *X*^2^ test will be used to compare the difference between groups, whereas the rank sum test will be adopted to analyze data when it belongs to ordered multinomial value. A two-sided *P* < 0.05 will be considered as significance for all statistical comparisons.

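### The withdrawal rule lets an NRS score of 6 or more, the entry level on the primary outcome scale, take participants out of the study, and sets all discontinued participants' data to missing

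*Protocol article*

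**What the plan says.** All references are to the protocol article.

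- **Inclusion criteria**, item 3, sets the entry level: "Average low back pain score ≥6 on a 0–10 numerical rating scale (NRS").
- **Primary outcome measurement** uses the same scale: "The primary outcome measure is the pain intensity of the low back assessed using an 11-point numerical rating scale (NRS"). Each score is the mean of a twice-daily diary kept for three days.
- **Outcomes** schedules assessments at baseline and at weeks 8, 12, 16, 24 and 36.
- **Withdrawal** has investigators evaluate, with a view to leaving the study, participants who "find their low back pain cannot be alleviated by acupuncture (base on a NRS score ≥6"), and those with serious adverse events. It adds that "participants can discontinue the treatment at any time for any reason", and closes with "All discontinued participants’ data will be treated as missing data".
- **Data collection and management** adds a further route after emergency unblinding: "Once unblinding occurred, the participant should be discontinued in the trial".
- **Statistical analysis** commits to intention to treat: "All data will be analyzed based on the intention-to-treat principle". Its rule for gaps in the record, given in the same sentence, reads: "including the missing data from dropouts which will be substituted into the collected data in the last assessment". That is last observation carried forward.

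**The concern.** Every participant enters at NRS 6 or more, so everyone starts at or above the number used to judge lack of relief. The number is a level and not a change: a participant who falls from 9 to 6 still sits on it.

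The Withdrawal section then merges two different events. Leaving the study ends data collection. Stopping acupuncture need not, because a three-day pain diary can still be completed. By treating the data of all discontinued participants as missing, directly after a sentence about stopping treatment, the plan gives up scores it could observe.

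The loss depends on the primary outcome. If active needling works as the sample size assumes, more sham than active participants will be at 6 or more, so the loss is also likely to differ between arms. Carry-forward then fixes these participants at the score they had when they stopped. The contrasts between electroacupuncture, manual acupuncture and sham at week 12 and in follow-up would depend partly on when and how often investigators use the rule. Intention to treat is meant to prevent this by following participants as randomised, whatever their adherence.

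**Working it through.** **1. The plan's own figure.** Sample size gives a difference of 1.5, SD 2.0, two-sided 5% and 90% power.

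- Normal approximation: n = 2 × (1.960 + 1.282)² × 2.0² / 1.5² = 37.4, so 38 per group.
- Noncentral t: power is 0.897 at 38 and 0.905 at 39, so the stated 39 per group is reproduced.
- With 20% dropout, 39 / 0.8 = 48.75, so 49 per group and 147 in total. The stated 144 is 48 per group. The gap of three is immaterial here.

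The sample size is not in dispute; it supplies the SD, the effect and the 20% loss allowance used below.

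**2. The rule step by step.** Entry at NRS ≥ 6 → lack of relief judged by NRS ≥ 6 → possible exit from the study → all data of the discontinued treated as missing → last assessment carried forward. Each step is stated in the text. No section read here provides for continued assessment after discontinuation.

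**3. How much it could matter at week 12 (illustration).** The document gives no post-treatment means, so these inputs are assumed:

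- Baseline normal (mean 7.3, SD 1.2), truncated to 6–10.
- Weeks 8 and 12: SD 2.0 (the plan's), scores clipped to 0–10.
- Sham week 12 mean 5.0, 5.5, 6.0 or 6.5; both active arms 1.5 lower (the plan's difference).
- 60%, 80% or 100% of the change reached by week 8.
- Week 8 to week 12 correlation 0.5 or 0.7; correlation with baseline 0.3.
- A participant with week 8 NRS ≥ 6 is discontinued with probability p, and the week 8 score replaces the week 12 score.
- 200,000 simulated participants per arm per scenario.

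The true difference, meaning the week 12 score had treatment and follow-up continued, is 1.46 to 1.49 after clipping.

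| p | Sham discontinued | Active discontinued | Week 12 difference after carry-forward | Relative to truth |
|---|---|---|---|---|
| 0.25 | 8–17% | 3–13% | 1.40–1.52 | −5% to +3% |
| 0.50 | 15–34% | 5–25% | 1.33–1.55 | −9% to +6% |
| 1.00 | 31–68% | 11–51% | 1.19–1.65 | −19% to +11% |

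The low ends arise when the sham mean stays high (6.5) and only 60% of the change is reached by week 8, because carry-forward keeps the smaller early gap. The high ends arise with lower sham means (5.0 to 5.5) and all the change reached by week 8: high scorers are frozen before they regress towards the mean, and there are more of them in the sham arm.

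**4. Sensitivity.** If the participant stops before any post-baseline assessment, the baseline is carried forward. The difference becomes 1.34–1.55, 1.21–1.60 and 0.96–1.70 for the three values of p.

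**5. A second set of assumptions.** With mean baseline 7, SD 2.0, correlation 0.6, week 12 falls of 3.0 (active) and 1.5 (sham), 50% to 100% of the effect reached by week 8 and p from 0.25 to 1.0, discontinuation is 4–40% in the active arms and 10–55% in sham. The carried-forward difference is 1.28–1.59, against about 1.48 with full follow-up. The pattern is the same: unequal loss, and bias in either direction.

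**The case against.** **The trigger is narrower than a score of 6.** The text asks investigators to evaluate participants who report no relief; the score sits in a parenthesis beside that. It may define non-relief or only set a floor. This stands as a limit on size: p = 1.00 is a bound, not a planning case. It does not remove the problem, because unspecified judgement then decides whose outcomes are lost, and the sentence on missing data leaves no discretion.

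**"Discontinued" may mean study leavers only.** The section speaks once of leaving the study and once of stopping treatment, and the analysis section refers to dropouts. Fig. 1 and Table 1 could not be read here and might show continued visits. This is a fair doubt about treatment stoppers. Even on the narrow reading, however, the protocol itself allows an exit from the study that is tied to the primary outcome.

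**The simulation does not measure what the fix would recover.** Its reference is the score had treatment continued; the fix would collect scores after treatment stops, possibly with other care. This stands. The ranges show how far the stated rule can move the estimate from that reference, not the exact bias removed.

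**Carry-forward does the simulated damage.** In the simulation, discontinuation depends only on the recorded week 8 score, so a likelihood-based repeated-measures analysis could handle it. This is correct, and the size should not be counted again under a separate point on carry-forward. In practice, decisions may also rest on complaints between visits that are not recorded as scores, and no analysis restores scores never collected.

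**At modest use the effect is small.** Only p = 0.25 keeps both arms within the planned 20% loss in every scenario. At its low end, the noncentrality is 1.40 / (2.0 × √(2/48)) = 3.43, and power with 48 per arm is still about 92%. This stands.

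**Emergency unblinding will be very rare.** Agreed; it adds little to the bias.

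**Conclusion.** The concern holds, as a stated rule that works badly and not as an omission. The plan ties exit from the study to a level on the primary outcome scale equal to the entry threshold, treats all discontinued participants' data as missing, and imputes the rest under an intention-to-treat label. Nobody is excluded from the analysis, but outcomes that could be observed are replaced, probably unequally between arms.

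The direction of the bias cannot be predicted. Its size depends on use of the rule: within about 5% of the week 12 difference at 25% use, within about 9% at 50%, and −19% to +11% if the rule is applied to everyone at NRS 6 or more. These figures rest on assumed means, correlations and timing of response; only the SD of 2.0 and the difference of 1.5 come from the plan. The conflict in the text does not depend on them. It should be fixed, because scores not collected after discontinuation cannot be recovered later.

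**What to change.** 1. In Withdrawal, separate stopping acupuncture from leaving the study. Anyone who stops treatment, whether for lack of benefit, an adverse event, unblinding or personal choice, stays on the week 8 to 36 assessments unless consent is withdrawn. Align the unblinding sentence in Data collection and management.
2. Replace the blanket missing-data sentence with a statement that all collected values are analysed in the randomised arm, and that only values not collected after withdrawal of consent or loss to follow-up are missing.
3. Ask the sponsor's clinicians to reconcile the stopping wording at NRS 6 or more with the identical entry criterion. Which clinical rule to keep is their decision; items 1 and 2 do not depend on it.

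The cost is a short protocol amendment and some follow-up visits after treatment stops, using existing staff and case report forms.

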### Data collection and management

Clinical data will be collected using the printed CRFs, which will be stored securely in a locked cabinet in the office at the hospital. Two independent investigators will enter the data into the clinical trial management platform ResMan and check for double entry to ensure the accuracy of data [29]. All electronic datasets will be de-identified and password protected. Both paper files and electronic documents are accessed to only authorized researchers. After verification, the database will be locked and delivered for statistical analysis. All original CRFs and consent forms will be kept strictly confidential and preserved for 10 years after publication. Only if there exists a life-threatening emergency event when it is a must to know the allocated intervention which participant has received, unblinding is permissible and the researcher can reveal the allocated details in the sealed envelope. Once unblinding occurred, the participant should be discontinued in the trial and the investigator should record the reason for the discontinuation in CRF.

### Monitoring

The trial will be conducted by the Shanghai Municipal Hospital of Traditional Chinese Medicine who will be responsible for coordinating, developing, and controlling the quality of all the programs. For the purpose of monitoring data, an independent Data and Safety Monitoring Board (DSMB) will be set up to review the trial data every month to ensure its accuracy and authenticity. The members of the DSMB who all have declared no conflict of interest in this trial will take the role of evaluating the safety of participants during the trial, monitoring the study progress, guaranteeing the accuracy and completeness of data, and providing recommendations to continuing, modifying, suspending, or terminating the study. Besides, any revisions of the protocol will be discussed by the ethics committee of Shanghai Municipal Hospital of Traditional Chinese Medicine timely.

### Sample size

The trial was aimed to determine whether there was a difference among the EA group, MA group, and SA group in terms of NRS scores. The sample size was calculated based on the previous study [30] through the PASS system (version 15.0.5), with the assumption of the difference in the mean NRS scores between the MA group and SA group as 1.5 and the standard deviation as 2.0. Thirty-nine participants per group would be required to provide 90% power with a two-sided significance level of 5%. Therefore, considering a 20% dropout rate, a total of 144 participants will be recruited eventually in the study.

### Statistical analysis

Statistical analyses will be performed using SAS (version 9.4) by an independent statistician totally blinded to the group allocation. All data will be analyzed based on the intention-to-treat principle, including the missing data from dropouts which will be substituted into the collected data in the last assessment. For measurement data, if the data is in conformity to normal distribution and homogeneity of variance, data values will be presented as mean ± standard deviation (*MD*±*SD*) and covariance analysis will be applied to compare data between groups. If the data does not comply with the normal distribution, median (P25, P75) will be adopted to describe it and the Mann-Whitney *U* nonparametric test will be applied for the comparison between groups. For categorical data, data can be presented as frequency, composition ratio, or rate on the basis of data results. When it comes to dichotomous or unordered multinomial data, the *X*^2^ test will be used to compare the difference between groups, whereas the rank sum test will be adopted to analyze data when it belongs to ordered multinomial value. A two-sided *P* < 0.05 will be considered as significance for all statistical comparisons.

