### Interventions

The interventions will be applied to eligible FBSS patients in three groups for 30 min for 24 sessions over 12 weeks (2 sessions per week). During the treatment, each patient will be placed in a separate quiet space and lying in the prone position, receiving one of the three treatments: electroacupuncture, manual acupuncture, or sham acupuncture. All the acupuncture procedures will follow the Standards for Reporting Interventions in Controlled Trials of Acupuncture (STRICTA) [20]. The location of acupoints for treating FBSS is shown in Fig. 2. In order to improve participants’ adherence, participants will accept the treatment for free and receive financial subsidies (200 RMB) after the last follow-up assessment.

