### Outcomes

The primary outcome will be pain intensity of low back. The secondary outcomes will be functional disability, depression symptoms, sleep quality, and analgesic consumption. All outcome data were collected at baseline, during the treatment phase (at 8 and 12 weeks), and at the 16-, 24-, and 36-week follow-ups.

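### Carrying the last assessment forward for dropouts can bias the arm comparison in either direction and can make an effect that has faded by week 36 look lasting

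*Protocol article*

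**What the plan says.** The Statistical analysis section claims intention-to-treat for all data, "including the missing data from dropouts which will be substituted into the collected data in the last assessment". The wording is awkward, but it can only mean that a missing value takes the participant's last collected value. No outcome or visit is exempted.

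Four other sections determine what this rule does:

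- Outcomes: after baseline, data are collected "during the treatment phase (at 8 and 12 weeks), and at the 16-, 24-, and 36-week follow-ups". Nothing is measured between baseline and week 8.
- Interventions: the 24 sessions end at week 12, so weeks 16, 24 and 36 are off treatment.
- Withdrawal: "Investigators will evaluate the participants who find their low back pain cannot be alleviated by acupuncture (base on a NRS score ≥6") or who have serious adverse events, with a view to discontinuation. The section adds: "All discontinued participants’ data will be treated as missing data".
- Sample size: the total of 144 is reached "considering a 20% dropout rate".

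**The concern.** LOCF assumes that pain stays where it was when the patient was last seen, and it gives the filled value the same weight as a measured one. Neither assumption suits this design. Entry requires an average NRS of at least 6, so anyone lost before week 8 re-enters every later comparison at a high, untreated score. Anyone last seen at week 8 or 12 contributes an on-treatment score up to 24 weeks after treatment ended (36 − 12). If benefit fades once needling stops, the fading is erased in those patients.

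The Withdrawal section adds two complications. Discontinuation is considered because of the primary outcome itself, so if treatment works more sham than active patients are likely to leave. Scores from patients who discontinue are also set to missing, which makes room for a carried value even where a real one might exist.

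At stake is any statement about durability at weeks 16 to 36 and, through early losses, the size of the contrast at week 12. The analysis as written cannot separate a lasting effect from a carried one.

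**Working it through.** **The plan's own figure.** Inputs from Sample size: difference 1.5, SD 2.0, two-sided 5%, 90% power. A two-sample t-test has 89.7% power with 38 per group and 90.5% with 39, so the stated 39 reproduces. Three groups give 117, and 117/0.8 = 146.25, against the stated 144 (48 per group). The gap is small and plays no part here. I use 48 per arm below.

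**Assumptions.** The protocol gives no pain course after treatment. I take the planned 1.5-point difference at both week 8 and week 12, SD 2.0, and a true difference of 0 at week 36.

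**Formula.** With equal random loss in both arms, the expected LOCF difference at week 36 is Σ pₖDₖ + (1 − Σpₖ)D₃₆. Here pₖ is the share last seen at visit k and Dₖ the true difference there. The standard error is about 2.0 × √(2/48) = 0.408. P(reject) ≈ Φ(d/0.408 − 1.96) + Φ(−d/0.408 − 1.96).

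1. *All loss just after week 12.* 20%: 0.20 × 1.5 + 0.80 × 0 = 0.30 points. Then 0.30/0.408 = 0.735 and rejection is 11.4% (simulation gives about 11%; complete data give about 5%). 10% loss gives 0.15 points and 6.6%. 30% gives 0.45 points and 19.7%.

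2. *20% spread evenly over the five intervals, linear fading.* D₁₆ = 1.5 × 20/24 = 1.25 and D₂₄ = 1.5 × 12/24 = 0.75. Each interval loses 4%, carrying in turn the difference at baseline (0), week 8, week 12, week 16 and week 24: 0.04 × (0 + 1.5 + 1.5 + 1.25 + 0.75) = 0.20 points. Then 0.20/0.408 = 0.490 and rejection is about 8%.

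3. *Pain-linked withdrawal.* Simulation with 48 per arm, means 6.0 (sham) and 4.5 (active) at weeks 8 and 12, a common week-36 mean of 6.0, correlation 0.5 or 0.7 between visits, and scores limited to 0–10. Each patient with NRS ≥6 at week 8 or 12 leaves with probability q.

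| q | Loss, sham / active | Spurious difference | Rejection |
|---|---|---|---|
| 0.2 | 19% / 9% | 0.14–0.17 | about 7% |
| 0.5 | 41–42% / 19–20% | 0.32–0.37 | 13–16% |
| 1.0 | 63–67% / 32–35% | 0.53–0.61 | 29–38% |

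Only the first row stays below the planned 20%. Mean carried scores were similar in the two arms (about 7.5 sham, 7.1 active at q = 0.2), so what differs is mainly how many leave. The result depends on the assumed week-36 mean: at q = 0.2, moving it from 7.0 to 4.5 moves the spurious difference from about 0.05 to 0.30.

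4. *The opposite direction.* If 20% of each arm were lost before week 8, all would carry baseline, where randomisation makes the expected difference 0. A true week-12 difference of 1.5 would be estimated as 0.80 × 1.5 = 1.20.

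**The case against.** The strongest reply is that the damage at the planned dropout is modest and rests on assumptions the protocol does not supply. Nothing in it says the effect disappears by week 36. The 0.30 requires every loss to fall just after week 12, and more ordinary timing gives about 0.20. This stands, and it is why the size is given as a range.

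Several stronger readings are tempting, and the protocol does not support them:

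- A reader might infer that false-positive rates of around a third are in prospect. That needs about half the patients in the two compared arms to leave, far above the planned 20%.
- A reader might infer that everyone with NRS ≥6 is removed. The protocol says only that such patients will be evaluated.
- A reader might infer that every dropout freezes an on-treatment score. Those lost before week 8 carry baseline, and those lost after week 16 or 24 carry a follow-up score.
- A reader might infer that LOCF is always biased when data are missing at random. It can be, but with stable means and loss unrelated to outcome the bias in the mean difference can be nil.

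It may also be said that a condensed article leaves detail to the full plan. That covers the absence of a sensitivity analysis, which carries no weight here. It does not cover LOCF, which the article itself fixes as the method.

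**Conclusion.** The point holds: LOCF is the stated rule for all data, and it is a poor choice for a trial with no assessment before week 8, 24 weeks of off-treatment follow-up, 20% expected dropout and discontinuation tied to the primary outcome. It can dilute a real effect or make a faded one look lasting.

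At losses up to about 20%, and if a 1.5-point difference at weeks 8 to 12 has gone by week 36, the spurious week-36 difference is roughly 0.15 to 0.30 points, with about 7% to 11% rejection instead of 5%. The pain-linked figure within that range also assumes a common week-36 mean of 6.0, and it falls to about 0.05 if that mean is 7.0. The direction of the bias in the actual trial cannot be known in advance. The protocol does not support saying that LOCF will produce a false durable benefit, only that it can.

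**What to change.** Amend the analysis before database lock and unblinding:

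- Make the main analysis a mixed model for repeated measures on all observed NRS values, with arm, visit, arm × visit, baseline NRS × visit and an unstructured covariance; or use multiple imputation.
- Change the Withdrawal wording so that outcome data obtained after treatment is stopped stay in the analysis instead of being set to missing. Without this the new model would still discard real observations.
- Add a reference-based or tipping-point sensitivity analysis for data not missing at random.
- Keep LOCF, if at all, as a labelled sensitivity analysis.

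The cost is rewording and some programming in SAS, which the protocol already names. The sample size is unchanged. The main model relies on data being missing at random given the observed scores. That is a weaker assumption than constant pain after dropout, and the sensitivity analysis tests it.

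### No primary visit or contrast is named for low back NRS while two-sided P < 0.05 applies to every comparison, so the 5% level behind the sample size does not hold for the trial's conclusion

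*Protocol article*

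**What the plan says.** The Primary outcome measurement section defines the measure without attaching a time to it: "The primary outcome measure is the pain intensity of the low back assessed using an 11-point numerical rating scale (NRS"). On timing, the Outcomes section lists baseline, weeks 8 and 12 within treatment, and weeks 16, 24 and 36 in follow-up. That gives five post-baseline values per patient, and neither section, nor the abstract, ranks one above the others.

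The article points to different contrasts in different places:

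- The Background presents the trial as evidence on EA against both MA and SA.
- For the NRS score, the Sample size section states a three-group aim: "The trial was aimed to determine whether there was a difference among the EA group, MA group, and SA group".
- The same section then sizes the trial on "the assumption of the difference in the mean NRS scores between the MA group and SA group as 1.5", with an SD of 2.0. That pair does not include EA. It concludes: "Thirty-nine participants per group would be required to provide 90% power with a two-sided significance level of 5"%.
- The Discussion concedes that power to separate MA from EA may be too low.

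The Statistical analysis section compares groups by analysis of covariance, or by the Mann-Whitney U test if the data are not normal. It closes with a rule for all tests: a two-sided P < 0.05 "will be considered as significance for all statistical comparisons".

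**The concern.** A 5% significance level describes one test, or a family of tests that is controlled as a whole. The sample size uses it for a single comparison of two means. The analysis section then grants the same 5% to every comparison, and the primary outcome offers several visits and several pairs of arms. Nothing in the article says which result decides whether EA worked.

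Two things are at stake. First, the chance of some false-positive finding on the primary outcome is well above 5%. Second, a reader of the results could not tell a result fixed in advance from one that stood out among many. This matters because the abstract says the outcomes will determine whether EA is efficacious, which is a confirmatory claim.

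**Working it through.** **Inputs from the article.** Three arms at 1:1:1; 144 patients, so 144 / 3 = 48 per arm; five post-baseline visits (weeks 8, 12, 16, 24, 36); two-sided 0.05 for each comparison; sizing difference 1.5, SD 2.0, power 90%.

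**Input assumed.** The correlation of NRS between visits is not in the article. It is taken as equal for all pairs of visits (exchangeable) and varied from 0.3 to 0.8.

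**Step 1: reproduce the plan's figure.** For a two-sample t-test with n per group, the noncentrality is 1.5 / (2.0 × √(2/n)). Power at two-sided 0.05 is 89.7% with n = 38 and 90.5% with n = 39. The stated 39 per group is therefore reproduced, as the size for one contrast at one time.

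**Step 2: count the tests.** The article gives no count, so it depends on the reading:

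- One three-group test per visit: 5 tests.
- Every pair at every visit: 3 × 5 = 15 tests, of which 2 × 5 = 10 involve EA.
- Every pair at one visit: 3 tests.

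**Step 3: upper bounds.** If k tests were independent, the chance of at least one false positive would be 1 − 0.95^k. This is 22.6% for k = 5 and 53.7% for k = 15. The second figure cannot be reached here, because the pairs share arms.

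**Step 4: simulate.** Normal data for 3 arms × 5 visits, 48 per arm, no true difference anywhere; t-tests for pairs and F-tests for three groups, each at 0.05 (40,000 replicates per setting). Chance of at least one false-positive primary result:

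| Correlation between visits | 0.3 | 0.5 | 0.7 | 0.8 |
|---|---|---|---|---|
| Five three-group tests | 21% | 18% | 15% | 13% |
| One pair over five visits | 21% | 18% | 15% | 12% |
| Ten pairwise tests with EA | 35% | 31% | 25% | 22% |
| Fifteen pairwise tests | 44% | 39% | 33% | 28% |
| Three pairs at one visit | 12% | 12% | 12% | 12% |

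Separate runs of the fifteen-test case gave 28% to 29% at correlation 0.8 and 44% to 45% at 0.3. It is quoted here as about 29% to 44%.

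**Step 5: cost of choosing versus correcting.** Naming one contrast at one visit leaves 39 evaluable per group sufficient under the stated assumptions. A Bonferroni correction with 39 per group would lower power to 80.4% for three contrasts at one visit (0.05 / 3) and to 61.1% for all fifteen (0.05 / 15).

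**The case against.** **The count of 15 is one reading only.** A reader might infer that the plan prescribes fifteen primary tests. It does not. The stated aim is a difference among three groups, and one analysis of covariance can compare three arms at once. On that reading there are five tests and the error rate is about half as large. This stands, so both ranges are given. It does not remove the problem: the lower range, 13% to 21%, is still more than twice 5%, and the fallback for non-normal data is a two-group test, which would have to be run by pairs.

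**An analysis plan may settle this.** The article condenses a fuller protocol, and a testing hierarchy is often left to the analysis plan. Silence alone would be no finding. Here, however, the article states a positive rule, 0.05 for all comparisons, and a plan that controlled the error rate would have to depart from it.

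**Intent.** A reader might also infer that the team will claim success from whichever visit or pair is significant. The article does not say so. What it shows is that nothing in its text prevents this.

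**MA versus SA as an implied primary.** It is the only contrast with a power calculation, but it is not called primary, has no visit attached and cannot answer the question about EA.

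**Pilot label.** The abstract and Discussion call the trial a pilot. Given a formal 90% power calculation and the stated efficacy aim, this gives little relief.

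**Conclusion.** The point holds and should be corrected before results are seen by arm. With no primary visit or contrast named and 0.05 applied to all comparisons, the 5% level used in the Sample size section does not describe the error rate of the trial's conclusion. Under no true effect, that rate is about 13% to 21% with five three-group tests and about 29% to 44% with fifteen pairwise tests; three pairs at one visit give about 12%. The ranges rest on 48 per arm, normal data and an assumed exchangeable correlation of 0.8 down to 0.3. The count of tests is derived from the design and is not stated in the article. The independence figure of 54% should not be quoted.

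The documents do not show that EA versus SA is underpowered. They show only that its power was never stated.

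**What to change.** Before unblinding, amend the Outcomes and Statistical analysis sections, and the registry entry to match, as follows.

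1. Name one primary visit. Week 12, the end of treatment, is a natural choice, though the article does not dictate it.
2. Name one primary contrast that answers the EA question: EA versus SA.
3. At that visit, test in fixed order, each at two-sided 0.05, stopping at the first non-significant result: EA versus SA, then MA versus SA, then EA versus MA. The last place suits EA versus MA because the Discussion concedes low power for it. Placed second, it would often block MA versus SA, the only contrast with a stated power basis.
4. Replace the rule of 0.05 for all comparisons. Report the other visits and the secondary outcomes as supportive estimates with confidence intervals.
5. State that the 90% power was calculated for MA versus SA, and that it carries over to EA versus SA only if the same 1.5-point difference and SD of 2.0 are assumed.

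The cost is a paragraph of wording and a registry update. No patients are added, and the first test keeps the full 0.05. The downside is that a later contrast can be claimed only if those before it succeed, and other visits can no longer support a claim of their own.
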